## Abstract

**Background:** Parenting interventions informed by attachment theory are an increasingly popular choice for clinical services that work with parents of babies and young children. Circle of Security Parenting (COS-P) is one such intervention, which has had extraordinary uptake internationally. Evidence for COS-P is very limited, however; there are few published studies, most with very small samples, and findings are mixed. This paper describes a multi-site evaluation of COS-P, designed to help address this evidence gap.

**Methods/Design:** This is a non-randomized controlled effectiveness study of COS-P in four community child and family health settings. Participants are caregivers of children aged 6 years and under, who present to study sites with parenting challenges in the early parenting period. Participants are recruited through these sites, and allocated to either treatment or waitlist control condition based on their capacity to attend the next available COS-P group. Outcomes (changes in caregiving attitudes and capacities linked to child social and emotional development, and caregiver depression symptoms) are assessed at baseline and post-treatment/waitlist using self-report questionnaires (all participants), and a narrative interview and 5-min parent-child interaction (a sub-sample of participants). Additionally, potential moderators of the intervention (demographic, symptom severity) will be tested.

**Discussion:** This is one of the first controlled evaluations of COS-P, and the first in Australia where COS-P dissemination has been particularly widespread. Results from this study will provide valuable information about the effectiveness of COS-P for caregivers with early parenting challenges, and will increase understanding of what works for whom.

## Introduction

Attachment theory (1–3) has informed thinking and practice in infant mental health for decades (4). It is also increasingly influential within the broader field of early childhood service provision (5). Parenting interventions based on attachment theory seek to improve the quality of the parent-child relationship and thus to improve the child's developmental trajectory, particularly with respect to social-emotional development. One of the most widely disseminated attachment-based interventions is Circle of Security Parenting (COS-P) (6, 7), an 8-week program that aims to build parenting capacity in parents of children aged from approximately 6 months to 6 years (7). COS-P is based on a more intensive 20-week Circle of Security protocol (8, 9), that allows individualized therapeutic work utilizing video feedback. COS-P was developed to facilitate broader implementation and uses stock DVD footage in place of individualized video material to demonstrate important concepts relevant to supporting secure attachment relationships (10). The centerpiece of both versions is a simple graphic (Figure 1), which captures the core dynamic at the heart of attachment theory regarding the child's need for both connection and exploration, and the caregiving behaviors that support these needs (11–13). Also fundamental to both versions is the therapeutic relationship between facilitator and participants (14).

**Figure 1 F1:**
[figure not shown]
Circle of Security circle graphic. Copyright 2016 by Cooper, Hoffman, and Powell. Reproduced with permission.

COS-P is broadly disseminated in North America, Europe, and Asia, and has proved particularly popular in Australia, where more than 10,000 COS-P facilitators had been trained by late 2016 (14). This figure will now be substantially higher, with more than 10 official COS-P training courses held around the country each year, often training more than 200 individuals at a time. Several state government departments and large non-profit organizations have adopted COS-P and/or the overarching COS model to inform their work with families of young children. Surprisingly, however, evidence for COS has not kept pace with dissemination (5), with remarkably few evaluation studies published to date for either version, precluding their endorsement as evidence-based programs by bodies like the influential California Evidence-Based Clearinghouse for Child Welfare (15).

Two studies of the intensive COS-I intervention with pre-post-designs have shown improvement in indices of child attachment in U.S. (13) and Australian (16) samples. The second of these studies also showed an increase in caregiver reflective functioning and caregivers' positive caregiving representations (16), improvements in child behavior problems and child social-emotional protective factors (17), and reductions in parenting stress and parent mental health symptoms (18). While these results are encouraging and in line with theory, they are limited by the absence of a control condition, small sample size, and the study context (single clinical setting).

To date, there are eight published studies evaluating the effectiveness of COS-P for parents. Five had very small samples (ns from 1 to 15). None of these included control or comparison groups and all but one used only self-report questionnaires to measure outcomes. Two were single case studies, the first of which showed post-COS-P improvements in parenting stress, perceptions of self-agency and child functioning, and parenting alliance (19). The second case study showed a reduction in attachment insecurity, anxiety and depression symptoms, and perceptions of child internalizing and externalizing behavior problems following COS-P (20). Two other studies (both *n* = 15) showed post-COS-P improvements in parents' self-reported emotion regulation, attributions about the child's behavior and discipline practices (21), and decreases in caregiver helplessness, feelings of fear, anger, and rejection toward the child, and levels of maternal stress (22). One study with a sample of opiate-dependent caregivers of young children (*n* = 8), reported a post-COS-P reduction in caregiver substance use and in depression, anxiety, and stress symptoms (23).

Three larger COS-P evaluation studies have been published recently. One was a multi-site evaluation of community delivery of COS-P (with no control or comparison group; *n* = 131), which focused primarily on the challenges of program delivery in a low socio-economic area in urban Connecticut, USA (24). Maupin and colleagues reported a reduction in caregiver depressive symptoms following COS-P, with a medium effect size, but no changes in caregiver reports of competency, reflective functioning, and the parent-child relationship. Significant implementation challenges were noted, including limited access to the resources needed to run groups (venue, printing facilities, computer equipment), failure to integrate COS-P into clinical caseloads, and limited clinical supervision.

Risholm Mothander and colleagues (25) reported results of a randomized trial (*n* = 52) examining COS-P plus treatment as usual (TAU), compared with TAU alone, in three Swedish infant mental health clinics. Parents in the COS-P group showed significant increases in balanced caregiving representations (interview measure) and in emotional availability (observational measure) 12 months after baseline. There was no significant change in outcome for the TAU-only group in the same period. However, differences between the two groups were not significant.

The largest COS-P study published to date is a randomized controlled trial (RCT) by Cassidy and colleagues (26). Findings were mixed and somewhat difficult to interpret. Analysis of complete data available for 141 mothers in a sample from the U.S. Head Start program, showed two significant main effects and some interesting moderation effects, all with small-medium effect sizes. Compared with the control group, mothers in the treatment condition reported a reduction in unsupportive responses to child distress and their children showed greater inhibitory control (a component of child executive functioning). There were no significant COS-P effects for child attachment security, as measured by the Strange Situation Procedure (SSP), or for parent-reported child behavior problems; however, for mothers with high attachment avoidance (self-reported), treatment group children scored higher on attachment security and lower on disorganization than control group children post-intervention. Those children whose mothers were low on self-reported attachment avoidance scored lower on attachment security than control group children post-intervention. In addition, treatment group children whose mothers scored low on self-reported attachment anxiety *or* low on depressive symptoms had fewer mother-reported internalizing behavior problems post-intervention than control group children (26). These mixed results should be interpreted with caution, given that the moderation analyses were necessarily exploratory due to study design. However, the indication that COS-P may result in greater attachment security and less disorganization in children of mothers who are high on self-reported avoidance is encouraging and warrants further investigation.

This RCT has clear strengths in its gold standard research design and use of multi-modal measures, including parent report as well as observations of child attachment and executive functioning. However, there are limitations in all COS-P studies to date and, viewed together, the findings are promising, but hardly compelling. This is clearly problematic in a context in which government provision of social service funding is increasingly dependent on funded programs being classified as evidence-based (27). Ongoing debate about what constitutes acceptable evidence (27, 28) notwithstanding, there is a clear need for further research with larger and more diverse samples. Moreover, given the extraordinary dissemination and public investment in COS-P training in Australia, there is an urgent need for research evaluating COS-P as it is delivered in these real-world contexts.

### Real World Research

While the RCT is the expected standard for generating evidence of causation (27, 29, 30), there is a growing awareness that evidence generated under laboratory conditions, while necessary, is not sufficient. RCTs often involve participants and environments so carefully controlled (to maximize internal validity) that they are unrepresentative of the real world, in which comorbidity and contextual complexity are the norm (30–35). The reduction of external validity to improve internal validity is partially offset by conducting RCTs in the field (36). However, the substantial time, financial, and staffing resources required to conduct an RCT (35) are beyond the capacity of many real-world settings. Furthermore, RCTs evaluating group interventions like COS-P are inherently more complex and thus even more resource-intensive than those evaluating individual treatments, due to requirements around group scheduling, minimum numbers, etc. (37). Even randomization itself is under scrutiny in psychological and social field research, with feasibility and suitability often questioned. As McCall and Green (2004, p. 8) contend, “publically funded services are never randomly assigned,” and parent choice and attendance at programs may be a key ingredient determining effectiveness. In light of these issues, there is increasing awareness of the need for evidence-*informed* practice (38), drawing on different levels and types of evidence (27, 30, 35, 39).

### Study Context

The current study developed out of a sustained period of engagement with COS-trained practitioners in Australia. The first step was a pilot survey of practitioners that aimed to investigate the dissemination and implementation of Circle of Security approaches and to identify unmet needs and key issues that required further research and/or evaluation. A link to an anonymous questionnaire was distributed to an email list of professionals who had completed any form of Circle of Security training: 614 respondents began the survey and 521 returned sufficient information for analysis. Of these, 455 (87.3%) had completed the COS-P 4-day training.

Key learnings from these survey responses were that the COS-P intervention was being offered in diverse ways (group/individual) to diverse populations, including families involved with the child protection system and families experiencing socioeconomic disadvantage, child behavioral challenges and/or parent mental health problems, in addition to parents in universal care settings. Responses indicated that COS-P was widely offered by services for women with postnatal depression (PND). Exploring the effectiveness of the intervention for women with PND is a key objective of the current study. The incorporation of COS-P into PND treatment protocols follows empirically-based recommendations that effective interventions for PND should include parenting-specific adjuncts to PND treatment. The well-documented adverse impacts of PND on the child and the parent-child relationship are believed to be predominantly mediated through impaired parenting (40–42) and studies of PND treatments have indicated that, while the mother's mood disorder can be successfully treated, remission of symptoms is not sufficient to improve parenting capacity or outcomes for children (43, 44).

COS practitioner survey responses also indicated that there was little systematic evaluation of COS-P in practice. Where evaluation was undertaken, it was mainly limited to informal observations and follow-up discussions with parents. When validated measures were used, the tools were mostly routine therapy outcome measures, such as mood state measures and the Strengths and Difficulties Questionnaire (SDQ) (45). Responses to open-ended survey questions further indicated that practitioners wanted guidance on: (a) which measures should be used to evaluate program effectiveness; (b) suitability and triage considerations for families with different risk profiles; and (c) compatibility and sequencing of the intervention in relation to other treatments being offered (e.g., treatments explicitly targeting depression). The current study seeks to address some of these issues.

### The Current Study

The primary aim of the current study is to examine the effectiveness of COS-P for caregivers who present to early parenting support services with parenting concerns, often in the context of PND. Study outcomes have been selected with reference to a recently developed theory of change for COS-P (46), which proposes that COS-P works to improve aspects of caregiving that may be necessary prerequisites for secure attachment, including caregiving representations (i.e., how the caregiver thinks and feels about the child, themselves as a caregiver, and their relationship with the child) and child-focused mentalization (the ability to be aware of and make inferences about mental states of self and child, and their impact on behavior). These components of relational caregiving capacity are theorized primary outcomes of COS-P. Changes in parent behavior, and in child attachment and/or behavior are not directly targeted by the intervention, but may be longer-term outcomes of targeted improvements in caregiving, and thus are considered secondary outcomes (46).

We aim to establish if COS-P is effective in building caregiving capacity through an increase in (a) positive representations of the child and self as caregiver, (b) more accurate caregiver mentalization, (c) more responsive caregiving behavior, and (d) reduction of caregiver depression symptoms. We hypothesize that caregivers receiving COS-P will show greater improvements in these areas than caregivers in a waitlist condition.

Given that COS-P research to date includes disparate (and often small) samples with a range of risk factors, we also intend to examine whether socio-demographic (e.g., caregiver language background, gender, education level, child age) and psychosocial (e.g., severity of depression symptoms) risk factors moderate response to the intervention, to extend knowledge of what works for whom. Due to limited empirical data available on COS-P outcomes, we do not posit directional hypotheses regarding the moderating effects of examined demographic and psychosocial risk factors.

In addressing these aims, we will trial a user-friendly evaluation tool assessing primary outcomes in line with the above COS-P theory of change, which may enable scaled measurement of COS-P outcomes through pooling of data from multiple sites. In addition, we will build research capacity within the study sites by training and supporting clinicians in research procedures, including participant recruitment and administration of study measures.

## Methods and Analysis

### Design

This study is a multi-site non-randomized controlled effectiveness study of COS-P, with treatment and waitlist control group participants undergoing assessment at two time points. The multi-site design both reflects the broad dissemination of COS-P and enables recruitment of sufficient participants to meet sample size requirements (see power analysis, below). The study design was determined in consultation with the study sites (see study setting, below); senior managerial staff indicated willingness to support incorporation of the study into their service, but maintained that they could not accommodate a randomized trial. Thus, participant allocation to treatment and waitlist control conditions will not be randomized, but dependent on the scheduled timing of the COS-P group in which they are enrolled. At study entry, participants whose COS-P group will commence within 7 weeks will be allocated to the treatment group. Participants whose COS-P group will commence eight or more weeks hence will be offered a place in the waitlist control group. Circumstances that may contribute to the latter include a long COS-P waiting list at the study site, registering just after a COS-P group has been filled or has started, inability to attend the next available group due to scheduling clashes, being assigned to a group that is subsequently canceled due to insufficient numbers, and the long gap between groups over the summer shutdown period. However, both treatment and control group participants must be determined to be “COS-P-ready” according to standard clinical procedure prior to their participation in the study. Waitlist control group participants will be free to engage with other forms of treatment or support within and outside of the organization prior to commencing the group. This study has been approved by the relevant university, health department and service-specific ethics committees (Macquarie University Human Research Ethics Committee: 5201600788; St John of God Healthcare Human Research Ethics Committee: 1153; Sydney Local Health District Ethics Review Committee: HREC/17/RPAH/285 & SSA/17/RPAH/432; ACT Health Human Research Ethics Committee: ETH.9.17.221E).

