### Study Setting

The study will be undertaken in collaboration with four community child and family health organizations (study sites) in two Australian cities located in separate states/territories. There are two study sites in each city. Three of these organizations have an explicit focus on perinatal mood problems, all offer COS-P in their suite of services for families with young children (aged 0-5) and all expressed an interest in participating in a collaborative evaluation study. See Table 1 for site details. All study sites routinely deliver COS-P groups, generally four times per year during school terms. All sites offer COS-P to current clients, and two also make the program available to parents from the community. One site delivers COS-P to clients only toward the end of other treatment, whereas the other three do not specify timing for the intervention. In all cases, group facilitators use their clinical judgement to assess suitability for the group, based on prior casework and/or a pre-group interview (face-to-face or by phone).

**Table 1 T1:** Overview of study sites.

	**Site 1 Tresillian Family Care Centres**	**Site 2 Raphael Services NSW St John of God Healthcare Social Outreach**	**Site 3 ACT Health Perinatal and Infant Mental Health Consultation Service**	**Site 4 Marymead Centre for Early Life Matters**
Type of service	Early parenting support	Perinatal and infant mental health	Perinatal mental health	Early parenting support
Referral pathway/s	•Health professionals •Self-referral for groups	•General practitioners and medical specialists	•Health professionals	•Health professionals •Education professionals •Self-referral
Accessed by parents with…	Parenting challenges, often around feeding, sleeping, settling, adjustment & associated perinatal mental health issues	Mental illness in the perinatal period (pre-conception to index child age 4)	Perinatal mood disorders (pregnancy to 12 months post-partum)	Concerns about parenting, adjustment, mental health, or child relationship, emotional, or behavioral issues
Child age range	0–5 years	Pre-conception to 4 years old	0–5 years	0–8 years
Professional staff	•Nurses •Social Workers •Psychologists •Psychiatrists/Registrars •Pediatricians •GPs	•Psychiatrists/registrars •Clinical Psychologists •Social Worker •Mental Health Nurses	•Medical Officer •Psychiatrists/Registrars •Psychologists •Social Workers •Occupational Therapists •Nurses	•Psychologists •Social Workers •Counselors

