Study measures will be administered by site clinicians and members of the research team, all of whom will receive related training and written instructions. Personnel administering measures in each case will depend on site capacity. Two study questionnaires will be administered to all study participants; interviews and observational procedures will be administered only to the subsample of participants who consent to and can complete these additional measures within the required timeframe. Treatment group participants will complete study measures a maximum of 2 weeks before the first session (Time 1) and a maximum of 2 weeks after the final session (Time 2) of their COS-P group. Those completing only study questionnaires will complete them at the relevant COS-P session (i.e., Time 1 at the start of session 1 and Time 2 at the end of session 8). Waitlist control group participants will complete both Time 1 and Time 2 study measures within the same 7 to 11-week timeframe, before they commence COS-P. Waitlist-control group participants completing only questionnaires will complete them onsite, if possible, otherwise they will be mailed hard copies or emailed individualized links to online versions of the Time 1 and Time 2 questionnaires. The latter process will be managed by the first author, using the university's password-protected Qualtrics platform. A separate record of individualized links by Client ID will enable matching of Time 1 and Time 2 data, and linking with clinical file data. De-identified questionnaire data for these participants will be stored securely in Qualtrics. All participants completing additional interview and/or observational procedures will complete these assessments at their study site or in their home, depending on site capacity, and participant convenience. For participants completing the observational assessment, time of day will be kept consistent between Time 1 and Time 2 assessments, to the extent possible considering parents' availability constraints and the unpredictability of infant/child sleep-wake cycles. See Figure 2 for study flow.

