### Data Analysis

Given that this is not a randomized trial, an intention to treat analysis is not essential. To maximize understanding of what works for whom, we seek to measure the intervention effect on those participants who actually receive the intervention—and we also seek to understand the factors that influence completion and non-completion of COS-P, as well as variations in response (71). Thus, data in this study will primarily be analyzed to measure the treatment effect on participants who received COS-P as intended. Complete Time 1 and Time 2 data for study participants who attend at least six of the eight COS-P sessions will be included in these analyses, together with data from clinical files and information collected during facilitator fidelity interviews, if appropriate. For participants who (a) attend 5 or fewer COS-P sessions and/or (b) do not complete Time 2 measures, treatment effect will not be measured; only Time 1 data, clinical file data and information collected during facilitator fidelity interviews will be analyzed, to explore whether characteristics of these caregivers distinguish them from completers and/or influence failure to complete the intervention.

Analyses will be conducted using SPSS Version 26 (72). Descriptive analyses will be used to profile and compare the characteristics of the treatment and waitlist control groups in the four participating sites. Bivariate correlations and independent samples *t-*tests will be used to explore relationships among the outcome variables and any potential covariates. As group allocation is not randomized, and recruitment is undertaken across four sites with different characteristics, the two groups may differ on distribution of demographic and risk factors which may impact on intervention effects. Baseline comparability will be assessed using independent samples *t*-tests (for continuous variables) and chi-square tests of independence (for categorical variables). Mixed design ANOVA will be used to control for any observed differences in baseline characteristics. Due to anticipated differences among participant cohorts from the four different sites, child age and depression symptoms (EPDS score at Time 1) will be included as *a priori* covariates. If sample size and composition allow, results will be stratified by site.

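### Some control measurement windows can span the summer shutdown while essentially no treated window can, and the stated adjustment does not address this partial link between calendar period and arm

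*Protocol article*

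**What the plan says.** All sections cited are in the protocol article.

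- **Design.** Arm is "dependent on the scheduled timing of the COS-P group in which they are enrolled". A start within 7 weeks means treatment. For later starts: "Participants whose COS-P group will commence eight or more weeks hence will be offered a place in the waitlist control group". Five circumstances that may lead to the longer wait are listed: a long list, a group just filled or begun, a scheduling clash, a cancelled group, "and the long gap between groups over the summer shutdown period".
- **Study Setting.** "All study sites routinely deliver COS-P groups, generally four times per year during school terms".
- **Procedure.** Treated participants who complete only questionnaires are measured at the group itself: "Time 1 at the start of session 1 and Time 2 at the end of session 8". Those with interview or video measures may be assessed up to 2 weeks before the first session and up to 2 weeks after the last. For controls: "Waitlist control group participants will complete both Time 1 and Time 2 study measures within the same 7 to 11-week timeframe, before they commence COS-P".
- **Data Analysis.** Child age and Time 1 EPDS are fixed covariates. Beyond these, "Mixed design ANOVA will be used to control for any observed differences in baseline characteristics". Results are stratified by site if numbers allow. No term for season, school term or calendar date is named.

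**The concern.** The effect of interest is the difference between arms in Time 1 to Time 2 change. That comparison is clean only if both arms would have changed alike without the programme. The plan matches the length of the two windows but not their position in the year. Because waiting over the shutdown is itself a route into the control arm, part of the control arm may be measured in a period from which treated windows are essentially absent.

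If mood, stress or self-rated caregiving shifts over that period, the shift enters the group-by-time term as if it were a programme effect. It could inflate or mask the true effect. Both questionnaires, the CCQ (primary) and the EPDS (secondary), are exposed. The position of the window is not a participant characteristic at baseline, so tests of baseline comparability would not reveal it.

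**Working it through.** **1. The plan's own interval.** Eight weekly sessions (Intervention) span 7 weeks from first to last. Adding up to 2 weeks at each end gives 7 + 2 + 2 = 11. The stated 7 to 11 weeks is reproduced, so duration is matched. The control wording is best read as the same duration, since nothing requires the control window to run alongside a treated group.

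**2. Whether a shutdown-route control can avoid the shutdown.** The article gives no calendar. Assume a 6-week break that ends when the next group starts.
- Avoiding the break entirely needs a wait of at least 7 + 6 = 13 weeks.
- At the 8-week threshold, a 7-week window leaves 8 − 7 = 1 week of slack, so at least 6 − 1 = 5 break weeks fall inside it.
- If the window ends at group start, break time is 6/11 = 55% to 6/7 = 86% of it. A longer wait lets the window sit elsewhere.

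**3. Treated windows.** For questionnaire-only participants, session 1 to session 8 lies wholly inside the group run. With interview or video measures, up to 4 of 11 weeks (36%) may lie outside it. Such a window can touch the edge of the shutdown by up to 2 weeks but cannot cross it.

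**4. Ordinary term breaks.** Assume 2-week breaks. A control window ending at group start then contains 2/11 = 18% to 2/7 = 29% break time. The 36% possible in the treated interview/video subsample exceeds this, so no consistent arm contrast exists for ordinary breaks. Only the summer contrast remains.

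**5. Size under assumptions.** Let q be the share of controls whose window spans the shutdown and s the seasonal shift in change, in SD units. With no treated window spanning it, the contrast moves by q × s. Take the planned 128, split 64 per arm (split assumed), so SE = √(4/128) = 0.177. Take a medium effect as 0.5 SD (assumed). The last two columns give the two-sided false-positive rate when the programme has no effect.

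| q | s (SD) | Shift q × s | Share of 0.5 SD | Nominal 0.05 | Nominal 0.005 |
|---|---|---|---|---|---|
| 0.10 | 0.1 | 0.01 | 2% | 0.050 | 0.005 |
| 0.25 | 0.2 | 0.05 | 10% | 0.059 | 0.007 |
| 0.50 | 0.3 | 0.15 | 30% | 0.136 | 0.025 |

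**6. Precision lost by excluding these controls.** Power for 0.5 SD with 64 treated against 64(1 − q) controls (two-sample comparison, normal approximation):

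| q dropped | Controls | Alpha 0.05 | Alpha 0.005 |
|---|---|---|---|
| 0 | 64 | 0.807 | 0.509 |
| 0.10 | 57.6 | 0.786 | 0.478 |
| 0.25 | 48 | 0.745 | 0.425 |
| 0.50 | 32 | 0.637 | 0.309 |

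These show relative loss only. The planned repeated-measures analysis has its own power, which depends on a correlation that the article does not state for the questionnaires.

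**The case against.** Four of the five listed routes to the waitlist do not depend on summer, so the affected share may be small. The documents do not show that anything relevant changes over the shutdown. The gap described is between COS-P groups. The safety section describes a case manager or clinician and routine monitoring for all participants, controls may use other support, and a chart audit records other services received. The Data Analysis section leaves room to explore further covariates, and the Discussion concedes unknown confounding. A condensed article may also leave such a check to a fuller plan.

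Much of this stands. A reader might infer that calendar period determines arm, that usual care or family routine is known to deteriorate over summer, or that the programme effect is therefore overstated. The documents support none of these: the link is partial, the mechanism is undocumented and the direction is unknown. Nor do they support extending the point to every school break, as step 4 shows.

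What survives is narrower. The shutdown route is named in the Design section, so it is a known feature and not an unknown confounder. The chart audit could describe service contact, but it is given no specific role in adjusting the group-by-time effect and would not capture mood. The stated covariates do not fit this feature of the allocation.

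**Conclusion.** The point holds as an inexpensive improvement; it is not an error or contradiction in the plan. Some control windows can span the summer shutdown, essentially no treated window can, and nothing in the stated adjustment addresses that. The size cannot be computed from the documents. Across the assumed values it runs from 0.01 SD, which can be ignored, to 0.15 SD, which would matter at either error level. These figures rest on an assumed share of controls, an assumed seasonal shift, an equal split of 128 and no treated window spanning the shutdown. Because the share is unknown, counting these controls is the first thing to do.

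**What to change.** Leave the main analysis unchanged and add the following.

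1. From the Time 1 and Time 2 dates, derive for each participant the number of weeks of the window that overlap the summer shutdown at that site. Define in advance what counts as spanning it, so that the edge overlap of up to 2 weeks possible in a treated window is kept apart from a window that crosses the shutdown.
2. Report the number of overlapping and spanning windows by arm and site.
3. State a sensitivity analysis of the group-by-time effect that excludes shutdown-spanning controls. This is preferable to a season covariate, which would extrapolate because there are essentially no treated windows in that period.

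The cost is one derived variable and some wording. The article does not say outright that assessment dates are kept, but its 2-week and 7 to 11-week limits cannot be applied without them. Precision falls in the sensitivity analysis (for example from 0.807 to 0.745 power at alpha 0.05 if a quarter of controls are dropped). Exclusion also changes the mix of waitlist reasons among the remaining controls. A difference from the main result should therefore be read as a robustness signal, not as proof of a seasonal effect.
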